## Abstract

**Background:** Hearing impairments are associated with reduced walking performance under Dual-task (DT) conditions. Little is known about the neural representation of DT performance while walking in this target group compared to healthy controls or younger adults. Therefore, utilizing the Mobile Brain/Body Imaging approach (MoBI), we aim at gaining deeper insights into the brain dynamics underlying the interaction of cognitive and motor processes during different DT conditions (visual and auditory) controlling for age and the potential performance decrements of older adults with hearing impairments.

**Methods:** The cross-sectional study integrates a multifactorial mixed-measure design. Between-subject factors grouping the sample will be age (younger vs. older adults) and hearing impairment (mild vs. not hearing impaired). The within-subject factors will be the task complexity (single- vs. DT) and cognitive task modality (visual vs. auditory). Stimuli of the cognitive task will vary according to the stimulus modality (visual vs. auditory), presentation side (left vs. right), and presentation-response compatibility (ipsilateral vs. contralateral). Analyses of DT costs and underlying neuronal correlates focus either on gait or cognitive performance. Based on an *a priori* sample size calculation 96 (48 healthy and 48 mildly hearing impaired) community-dwelling older adults (50–70 years) and 48 younger adults (20–30 years) will be recruited. Gait parameters of speed and rhythm will be captured. EEG activity will be recorded using 64 active electrodes.

**Discussion:** The study evaluates cognitive-motor interference (CMI) in groups of young and older adults as well as older adults with hearing impairment. The underlying processes of the interaction between motor and cognitive tasks will be identified at a behavioral and neurophysiological level comparing an auditory or a visual secondary task. We assume that performance differences are linked to different cognitive-motor processes, i.e., stimulus input, resource allocation, and movement execution. Moreover, for the different DT conditions (auditory vs. visual) we assume performance decrements within the auditory condition, especially for older, hearing-impaired adults. Findings will provide evidence of general mechanisms of CMI (ST vs. DT walking) as well as task-specific effects in dual-task performance while over ground walking.

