### Aims and Research Questions for the Study

The present study is designed to investigate the following three foci using a MoBI approach:

Focus 1: General characteristics of dual-task walking of all participants.

•How does cognitive task performance differ when using visual or auditory stimuli in single- and dual-task conditions?•How are dual-task costs represented in gait parameters?•How are neuronal correlates of auditory and visual information processing impacted by dual-task interference during walking?

Focus 2: Age-related differences in dual-task walking.

•Can we replicate the age-related increase in dual-task costs?•How are the age-related differences in performance reflected in the respective brain activity of younger and older adults?•How do younger and older adults differ in their gait parameters and gait-phase related stimuli processing?

Focus 3: Differences of hearing-impaired and healthy older participants in dual-task walking.

•How do auditory vs. visual information processing and movement control vary with regards to the effect of hearing impairment represented in both cognitive task stimuli modalities and dual-task vs. single-task performance?•How are dual-task costs reflected in biomechanical and neuropsychological measures of hearing-impaired participants?

The overall hypothesis is that there are differences in dual-task costs and their corresponding neuronal correlates between the three groups with the highest disadvantages for the group of older adults with impaired hearing. We hypothesize that the performance differences are linked to the different cognitive-motor processes; i.e., information or stimulus input, resource allocation, and movement execution. Further, we hypothesize that the increasing task complexity (from single-task to dual-task), as well as the stimulus modality (visual vs. auditory), will further diminish the walking performance and increase neuronal activity.

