### Trial Design

This protocol will reflect a multifactorial mixed-measure design with the two two-level between-subject factors, *age* (younger vs. older adults) and *hearing impairment* (mild hearing-impaired vs. not hearing impaired). The design will be incomplete as the sample contains older adults with hearing impairments and healthy controls matched by age and gender as well as a younger age group. No data of young hearing-impaired adults will be recorded.

The within-subject factors will be the *task condition* (single- vs. dual-task) and *cognitive task modality* (visual vs. auditory). Stimuli of the cognitive task will vary according to the *presentation side* (left vs. right), *modality-specific properties* (magenta vs. cyan or low vs. high pitch, respectively), and *presentation-response compatibility* (ipsilateral vs. contra-lateral). Analyses of dual-task costs and underlying neuronal correlates can focus either on gait parameters or cognitive task performance.

The chosen colors and tone pitch levels are the conclusion of extensive piloting. In case further testing reveals that other properties are more appropriate for the experimental paradigm, we keep the option open to change the modality-specific properties.

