#### Recruitment of Participants

To assure eligibility and recruitment of participants, community-dwelling older adults will be recruited from a database of the TU Berlin (e.g., “TUB-Versuchspersonenportal”) as well as public advertisement and collaborating audiologists in the surrounding areas of Berlin and Hamburg.

Based on sample size calculation (for details see section “Sample Size Estimate/Power Calculations”), a group of 96 community-dwelling older adults (50–70 years) and 48 younger adults (20–30 years) will be recruited. The older experimental group will be divided into the following 2 equally sized subgroups: (1) hearing impaired, (2) not hearing impaired. The participants’ allocation to the group will be done after prior assessment using a test battery in a first session. Data analyses will be done on anonymized data.

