#### Statistical Analysis

Descriptive data will be presented as mean (*M*) and standard deviation (*SD*). Normal distribution and homoscedasticity will be checked by the Shapiro-Wilk-Test and the Levene-Test, respectively. Dual-task costs will be analyzed using univariate analyses of variances (ANOVA) including the between-subject factors *age* (younger vs. older) and in case of older *hearing ability* (hearing impaired vs. non-hearing impaired) and the within-subject factors *task complexity* (single- vs. dual-task) and *stimulus modality* (visual vs. auditory).

Significance will be set at α = 0.05. The effect size will be presented as partial eta squared. In all *post hoc* comparisons we will control for multiple comparisons (e.g., Bonferroni). Statistical analyses will be done by using SPSS (IBM, SPSS Inc., Chicago, IL, United States) or R (R Core Team, 2013).

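### As worded, the age factor can set younger adults against an older group that is half hearing-impaired; the Focus 2 age effect may then include half of the hearing effect

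*Protocol article*

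**What the plan says.** The Abstract sets the group sizes: "96 (48 healthy and 48 mildly hearing impaired) community-dwelling older adults (50–70 years) and 48 younger adults (20–30 years) will be recruited". Recruitment of Participants confirms the even split: "The older experimental group will be divided into the following 2 equally sized subgroups".

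Trial Design describes age and hearing impairment as two between-subject factors with two levels each, and then says: "The design will be incomplete as the sample contains older adults with hearing impairments and healthy controls matched by age and gender". It adds: "No data of young hearing-impaired adults will be recorded". Three of the four cells are therefore filled.

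Statistical Analysis plans ANOVAs of dual-task costs. The between-subject part is age, "younger vs. older) and in case of older" adults hearing ability as well. The within-subject factors are task complexity and stimulus modality. On the error level it says: "Significance will be set at α = 0.05".

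The age question is Focus 2 in Aims and Research Questions: "Can we replicate the age-related increase in dual-task costs". The overall hypothesis in that section expects differences between three groups, "with the highest disadvantages for the group of older adults with impaired hearing". No section names younger vs normal-hearing older adults as the test for Focus 2.

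**The concern.** Focus 2 is about ageing and Focus 3 about hearing loss. To keep them apart, the age comparison must hold hearing constant, and the only older group that allows this is the normal-hearing one. The analysis section does not name that comparison. It sets younger against older and brings in hearing only inside the older level, where one participant in two is hearing-impaired because recruitment was set up that way.

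On that reading the age term mixes both effects. For dual-task cost, the primary outcome, the study's own hypothesis pushes them in the same direction, so hearing loss would be counted as ageing. The age-by-task and age-by-modality terms are affected in the same way. The latter matters because the Discussion expects the auditory decrement to be greatest in the hearing-impaired group.

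**Working it through.** **Inputs from the documents.** Three groups: younger (Y), older normal-hearing (ONH) and older hearing-impaired (OHI). They are recruited 48:48:48; the sample size section plans for 36 per group. Two-sided α = 0.05.

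**Assumptions.** The article gives no hearing effect, so I take H = 0.2, 0.5 and 0.8 SD. I use one dual-task cost value per participant, a common residual SD of 1, and a true age effect of zero to isolate the leakage. The article states no figure for the age contrast itself, so there is none to reproduce. I use 36 and 48 per group only as sizes.

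**Step 1: what the age term estimates.** Let A = ONH − Y and H = OHI − ONH, in group means.

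- Pooled or nested, equal older groups: (ONH + OHI)/2 − Y = A + H/2.
- Crossed main effects, age adjusted for hearing: ONH − Y = A.

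Least-squares fits at 48 per group with A = 0 confirm this:

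| H | age entered alone | hearing nested in older | crossed, partial sums of squares |
|---|---|---|---|
| 0.5 SD | 0.25 | 0.25 | 0 |
| 1.0 SD | 0.50 | 0.50 | 0 |

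With unequal completers, for example 40 ONH and 32 OHI, the hearing share in the pooled fit is 32/72 = 0.444. In the nested fit it stays at 0.50.

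**Step 2: one data set, two age tests.** Take 48 per group, A = 0, H = 0.5. With age entered first, the age sum of squares is 0.25² / (1.5/48) = 2.0, so F = 2.0 on 1 and 141 df (p = 0.16). With partial sums of squares it is 0. The hearing term is the same in both (F = 6.0, p = 0.016).

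**Step 3: rejection rate of the age test when A = 0.**

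SE = √(1/n + 1/(2n)) = √(1.5/n), which is 0.204 at n = 36 and 0.177 at n = 48. The noncentrality is (H/2)/SE. The rate comes from the noncentral t with 3n − 3 df (105 and 141).

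| H (assumed) | noncentrality, n = 36 | rate, n = 36 | noncentrality, n = 48 | rate, n = 48 |
|---|---|---|---|---|
| 0.2 SD | 0.49 | 8% | 0.57 | 9% |
| 0.5 SD | 1.22 | 23% | 1.41 | 29% |
| 0.8 SD | 1.96 | 49% | 2.26 | 61% |

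For scale, suppose a between-group effect of the planned size f = 0.25 came only from the hearing-impaired group. Then H = 0.25 × 3/√2 = 0.53 SD, and the rates are 25% and 32%.

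**Step 4: interactions.** Replace each group mean by the group mean of a within-person difference (dual minus single task, or auditory minus visual). The algebra is unchanged: the age-by-task term carries half the hearing-by-task effect, and the age-by-modality term half the hearing-by-modality effect.

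**Step 5: the clean contrast.** Y vs ONH has SE √(2/n), which is 0.236 at n = 36 and 0.204 at n = 48. The ratio to the pooled contrast is √(2/1.5) = 1.155.

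**The case against.** The strongest reply is that the text does not commit to the contaminated contrast. Trial Design describes two two-level factors in a design it openly calls incomplete. Entered as crossed main effects with partial sums of squares, they give an age term free of the hearing effect. That stands. A reader might infer that the planned age effect necessarily contains half of the hearing effect; the documents do not support that. They support the narrower statement that the more natural reading of the analysis section gives that result and nothing excludes it.

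The article also often treats the sample as three groups: in the overall hypothesis, in the sample size calculation and in the Discussion. It allows corrected post hoc comparisons, among which younger vs normal-hearing older could appear. This shows that the clean contrast is within reach, but does not make it the Focus 2 test. Unnamed post hoc comparisons do not prevent the pooled main effect from being reported as ageing.

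The type of sums of squares is a detail that an article may leave to a fuller plan, and its absence alone is no fault. The point rests on the factor structure that the article does state.

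Finally, the higher rejection rates assume a medium or large hearing effect and no age effect at all. The impairment studied is mild, Focus 2 presupposes an age effect, and 48 per group is the number aimed for at prescreening. All of that is fair. With H = 0.2 SD the rate is only 8–9%. If age does matter, the consequence is an overestimate rather than a false positive.

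**Conclusion.** The concern holds in a conditional form. With hearing nested in the older level, or with age entered first and sequential sums of squares, the Focus 2 age term is A + H/2; with age adjusted for hearing in a crossed main-effects model, it is A. The plan leaves open which applies. The one-half follows exactly from the even split of the older sample and needs no assumption about effect size.

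The error rates do rest on assumptions: 8% to 49% at 36 per group and 9% to 61% at 48, for H from 0.2 to 0.8 SD with no age effect. They show sensitivity and do not forecast what this study will find.

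For dual-task cost the likely direction is overstatement of the age effect, because the plan expects the hearing-impaired group to do worst. This need not carry over to every EEG measure. The Discussion expects a dual-task reduction of the late positive complex in the young but not in the old, and less of it in normal-hearing than in hearing-impaired older adults. There, pooling would dilute the age difference.

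One of the three foci depends on this contrast, so its meaning should be fixed before analysis.

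**What to change.** In Statistical Analysis, replace the two between-subject factors by one group factor with three levels and name two pre-planned contrasts:

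- Focus 2 (age): younger vs older normal-hearing.
- Focus 3 (hearing): older hearing-impaired vs older normal-hearing.

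Apply both contrasts to the interactions with task complexity and stimulus modality, and bring the factor description in Trial Design into line. State that the pooled younger vs older difference will not be reported as an age effect.

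Recruitment and measurements stay as they are, and the sample size section already counts three groups. The cost is precision: the age contrast uses 48 + 48 rather than 48 + 96 recruited participants, so its standard error rises by about 15%.

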#### Sample Size Estimate/Power Calculations

A g^∗^power sample size calculation (*a priori*: *F*-tests; repeated measures, within-between interaction, effect size f = 0.25; alpha error prob = 0.05; power (1-beta error prob) = 0.8; number of groups = 3) revealed a total of *N* = 36 for each group. Due to an expected drop-out rate of about 20 percent, we will integrate at least 44 participants for each group. We aim to recruit 48 participants per group for the Prescreening.

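### Holm's procedure would control post hoc error as well as the Bonferroni example the plan gives, and is never less powerful

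*Protocol article*

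**What the plan says.** The Statistical Analysis section sets the level: "Significance will be set at α = 0.05". The model is an ANOVA with within-subject factors for task complexity and stimulus modality. Its between-subject factors are age ("younger vs. older) and in case of older" participants, hearing ability). For what follows the ANOVA, the section says: "comparisons we will control for multiple comparisons (e.g., Bonferroni". No other adjustment method is named, and the post hoc families are not listed.

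The sample size section sizes the study on an F test described as "repeated measures, within-between interaction", with "effect size f = 0.25; alpha error prob = 0.05; power (1-beta error prob) = 0.8; number of groups = 3". It arrives at "36 for each group". It makes no power statement for any adjusted pairwise comparison.

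**The concern.** The study's hypothesis is about differences between three groups, with hearing-impaired older adults worst off. A significant group effect or group-by-condition interaction does not show which groups differ, so some post hoc comparisons are likely. In a family of three pairs, Bonferroni tests each one at 0.05/3 = 0.0167, however clear the other results are. Holm relaxes that threshold once a comparison has been rejected, and the familywise guarantee stays intact. What is at stake is power in the follow-up tests; validity is not in question.

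**Working it through.** **Inputs.** From the article: alpha 0.05, three groups, 36 per group. Assumed: two-sided tests, normal outcomes with equal variances, and differences in SD units (the article gives none for pairwise contrasts).

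The 36 per group is taken as given. The number of measurements, their correlation and the sphericity correction are not stated, so it cannot be reproduced uniquely. With three measurements, for example, correlation 0 and epsilon 0.5 give 108 in total (36 per group), while correlation 0.5 and epsilon 1 give 36 in total. Neither result depends on the post hoc method.

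**Step 1: why Holm is never less powerful.** Order the three p-values. Holm compares them in turn with 0.05/3 = 0.0167, 0.05/2 = 0.025 and 0.05, and stops at the first failure. No threshold is below 0.0167, so any comparison that Bonferroni rejects is also rejected by Holm.

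**Step 2: why the error control is the same.** Suppose k of the three null hypotheses are true. The first true null in the ordering meets a threshold of at most 0.05/k. A false rejection therefore needs one of k p-values to be at or below 0.05/k, and the Bonferroni inequality bounds that at k × 0.05/k = 0.05. Independence is not needed. The argument holds for a family of any size, so it also covers follow-up of interactions.

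Simulation of three equal normal groups of 36 (200,000 runs per setting) agrees:

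| Truth | Any false rejection, Bonferroni | Holm |
|---|---|---|
| All groups equal | 4.3% | 4.3% |
| One true null pair | 1.7% | 2.6% |

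**Step 3: bounds on the gain.** For one pair at 0.5 SD, the noncentrality is 0.5 × √(36/2) = 2.12. By the normal approximation, power is:
- at 0.0167: Φ(2.12 − 2.39) ≈ 39%
- at 0.025: Φ(2.12 − 2.24) ≈ 45%
- at 0.05: Φ(2.12 − 1.96) ≈ 56%

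Holm must lie between the first and the last. Its position depends on how often the other pairs are rejected first.

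**Step 4: size of the gain.** Simulated power for the age or hearing pair, three-pair family, t tests:

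| Group means (young, older, older impaired), SD | n per group | Bonferroni | Holm |
|---|---|---|---|
| One of the two differences real, 0.5 | 36 | 38% | 41% |
| One real, 0.7 | 36 | 70% | 74% |
| Equal steps of 0.31 | 36 | 13% | 17% |
| Equal steps of 0.5 | 36 | 38% | 49% |
| Equal steps of 0.66 | 36 | 64% | 78% |
| One real, 0.5 | 44 | 47% | 50% |
| Equal steps of 0.5 | 44 | 47% | 60% |

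The gain at 0.5 SD is 41 − 38 = 3 points with one real difference and 49 − 38 = 11 points with equal steps. It is larger with equal steps because the young versus hearing-impaired pair, at 1.0 SD, is nearly always rejected first. The other two pairs then face 0.025 or 0.05.

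If the family held only the age and hearing pairs, Bonferroni and Holm would both give 44% with one difference real. With both real they would give 44% and 49%.

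**The case against.** The strongest reply is that nothing here is wrong. Bonferroni is valid and appears only as an example, so Holm already satisfies the sentence. The exact procedure may also be fixed in an analysis plan that is not shown. All of this stands, and it is why the point is an optional improvement. Bonferroni also has one real advantage: it yields simple simultaneous confidence intervals.

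A reader might infer that the age and hearing questions themselves are tested at a third of alpha. The article does not support that. Both the Trial Design and Statistical Analysis sections enter age and hearing as two-level factors. Each such factor has its own F test at 0.05, and the text does not place those tests under the post hoc adjustment. For them the change gains nothing.

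A reader might also prefer the three-group closed test: an overall F test at 0.05, then each pair at 0.05. It does hold the familywise error, and it beats Bonferroni in the three-pair setting. But with 36 per group and only the hearing difference real at 0.5 SD, its power for that difference is about 48%. An ungated hearing test at 0.05 has about 55%. The overall F test also relies on equal variances. The shortcut is specific to three group means and does not carry over to follow-up of the group-by-condition interactions on which the study is sized.

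**Conclusion.** The point holds as an efficiency improvement: for any post hoc family, Holm gives the protection that Bonferroni gives and never rejects less. The gain is modest. It is about 3 to 4 points when only one of the age and hearing differences is real, and about 4 to 14 points with equally spaced groups, over the effect sizes tried at 36 per group. In a family of only the age and hearing pairs it is about 0 to 5 points at 0.5 SD. These sizes rest on assumed SD effects, normal outcomes with equal variances, and a single outcome rather than the full repeated-measures model. The dominance of Holm rests on none of those. No stated figure changes, and the article gives no ground for saying that the age and hearing factor tests lose alpha.

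**What to change.** In the Statistical Analysis section, replace the Bonferroni example with wording such as: post hoc comparisons will be Holm-adjusted within each family of post hoc comparisons; the prespecified two-level tests of age and hearing ability remain at alpha 0.05. Naming one method also removes the choice that the present example leaves open until the data are seen.

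The cost is one sentence. Holm is available in R, which the plan already names, and no extra participants or data are needed. If simultaneous confidence intervals are to be reported, state that they will be Bonferroni intervals and may be more conservative than the Holm tests.

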#### Sample Size Estimate/Power Calculations

A g^∗^power sample size calculation (*a priori*: *F*-tests; repeated measures, within-between interaction, effect size f = 0.25; alpha error prob = 0.05; power (1-beta error prob) = 0.8; number of groups = 3) revealed a total of *N* = 36 for each group. Due to an expected drop-out rate of about 20 percent, we will integrate at least 44 participants for each group. We aim to recruit 48 participants per group for the Prescreening.

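### The sample-size figure of 36 is given as both a total and a per-group number, and 36 per group does not follow from the named interaction test under G*Power's default convention

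*Protocol article*

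**What the plan says.** The Sample Size Estimate/Power Calculations section describes an a priori G*Power calculation for an F-test: "repeated measures, within-between interaction, effect size f = 0.25; alpha error prob = 0.05", with "power (1-beta error prob) = 0.8; number of groups = 3". The sentence introduces its result as a total N and ends with "36 for each group". It continues: "Due to an expected drop-out rate of about 20 percent, we will integrate at least 44 participants for each group". The recruitment target follows: "We aim to recruit 48 participants per group for the Prescreening". The section does not give the number of repeated measurements, their correlation, epsilon or the effect-size convention, and it does not name the outcome to which f = 0.25 applies.

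The overall hypothesis, under Aims and Research Questions for the Study, is that "there are differences in dual-task costs and their corresponding neuronal correlates between the three groups". Primary Outcomes names dual-task cost. The Introduction defines it as a ratio: single-task minus dual-task performance, divided by single-task performance. Statistical Analysis plans univariate ANOVAs of dual-task costs, yet keeps single- versus dual-task, as well as modality, as within-subject factors.

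**The concern.** One number cannot be both the total over three groups and the size of each group. The two readings, 36 and 108 participants, differ threefold. Because the test, effect size, alpha, power and number of groups are all printed, a reader can check which reading fits. The default calculation returns the total and not the per-group figure.

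The plan also leaves open what the 80% refers to. A dual-task cost already contains the single- versus dual-task contrast, so that contrast cannot also be a factor in an analysis of the cost. Two analyses remain possible: a group × task interaction on raw performance, or a group comparison of the ratio score. At 36 per group they have very different power for the same nominal f. At stake is how a null result would be read, especially for hearing loss: the printed 0.80 would be taken as the power of whichever comparison is reported.

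**Working it through.** **Inputs stated in the plan:** f = 0.25, alpha = 0.05, target power 0.80, k = 3 groups; 36, 44 and 48 per group; 20% drop-out.

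**Inputs assumed because they are not stated:** m = 2 to 4 (the 2 × 2 within-subject structure suggests 2 or 4; three walking conditions would give 3), rho = 0 to 0.7, epsilon = 1 unless noted. N is raised in steps of 3 to keep the groups equal.

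**1. Reproducing 36.** For the within-between interaction under the default convention, power comes from the noncentral F with lambda = f²·N·m·epsilon/(1 − rho), df1 = (k − 1)(m − 1)·epsilon and df2 = (N − k)(m − 1)·epsilon.

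At m = 3, rho = 0.5, N = 36: lambda = 0.0625 × 36 × 3/0.5 = 13.5, df 4 and 66, power 0.823. At N = 33 power is 0.781. So 36 is reproduced exactly, as a total (12 per group).

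Total N for 80% power:

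| m | rho = 0 | rho = 0.3 | rho = 0.5 | rho = 0.7 |
|---|---|---|---|---|
| 2 | 81 | 60 | 42 | 27 |
| 3 | 69 | 48 | 36 | 24 |
| 4 | 57 | 42 | 30 | 21 |

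The largest entry is 81 (27 per group). None is 108.

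**2. Power of the named test at 36 per group (N = 108).**
- m = 2, rho = 0: lambda = 0.0625 × 108 × 2 = 13.5, df 2 and 105, power 0.911.
- m = 2, rho = 0.5: lambda = 27, power 0.998.
- m = 3, rho = 0.5: lambda = 40.5, power above 0.999.

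**3. A test that does return 108.** For the between-groups effect, lambda = f²·N·m/(1 + (m − 1)·rho). At m = 3, rho = 0.5, N = 108: 0.0625 × 108 × 3/2 = 10.125, df 2 and 105, power 0.809.

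**4. Unreported settings that bring the interaction near 108.**
- f derived from partial eta squared, with lambda = f²·(N − k)(m − 1) or f²·N·(m − 1): 99–102 in total at m = 3, and 159–162 at m = 2.
- Default convention with m = 3, rho = 0, epsilon = 0.5: lambda = 0.0625 × 108 × 3 × 0.5 = 10.125, df 2 and 105, power 0.809, so N = 108.

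**5. Group comparison of the ratio dual-task cost at f = 0.25, N = 108.** The formula is that of step 3, with f on the scale of a single score.
- One score (m = 1): lambda = 0.0625 × 108 = 6.75, power 0.625. Reaching 80% takes N = 159 (53 per group; lambda = 9.94, power 0.805). At N = 108, 80% power is reached at f = 0.30.
- Mean of two modality scores (m = 2): lambda = 10.4, 9.0 and 7.9 at rho = 0.3, 0.5 and 0.7, giving power 0.82, 0.76 and 0.70.
- Older hearing-impaired versus older normal-hearing, two-sample t-test with 36 per group: detectable d at 80% power is 0.67, or 0.78 at alpha 0.05/3 (Bonferroni for three pairs).

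**6. Drop-out.** 36 × 1.2 = 43.2, rounded up to the plan's 44. Keeping 36 after 20% loss takes 36/0.8 = 45, since 44 × 0.8 = 35.2. Recruiting 48 leaves 48 × 0.8 = 38.4.

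**The case against.** The best defence is that the inputs are incomplete rather than wrong, and an article may leave m, rho and epsilon to a fuller document. A reader might infer from the default results that the named interaction can never need 36 per group. That is too strong. Statistical Analysis reports effects as partial eta squared, and with f derived from that measure the requirement at m = 3 is about 99–102, with power at 108 of roughly 0.83–0.84. A reduced epsilon can give 108 itself. This part of the objection stands: the mismatch is shown for the default convention with sphericity. The plan reports none of these other settings, however, and they do not resolve a figure that is both a total and a per-group number.

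A reader might also infer that the wrong test family was named. The documents do not support that. If raw performance is modelled, the group × task interaction is itself the comparison of absolute dual-task cost between groups. Under the default convention, though, f = 0.25 at m = 2 and rho = 0.5 corresponds to 0.25 × √(2/0.5) = 0.5 on the difference score, a large effect, and power at 36 per group is 0.998.

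Finally, a reader might infer that the trial is underpowered at 0.63. That is the least favourable reading: one score, no modality factor, and f = 0.25 carried over to a different quantity. Averaging the two modality scores gives 0.70 to 0.82, which includes 0.80. The pairwise detectable effects concern a contrast that the plan never claimed to power. They are useful to report but do not show an error.

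**Conclusion.** The point holds in a bounded form. The result is worded contradictorily and, under G*Power's default convention with epsilon = 1, does not follow from the stated test: 30–42 in total at rho = 0.5, at most 81 at rho = 0, against 108 implied by 36 per group. On that basis power for the named interaction at 36 per group is 0.91 to above 0.99. For the ratio dual-task cost at f = 0.25 it is 0.63 (one score) or 0.70–0.82 (mean of two, rho 0.7 to 0.3). The stated 0.80 is met only under particular settings that the plan does not report.

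A total misread as a per-group figure would explain the number, and so would a calculation for the between-groups effect. The documents do not show which occurred. Nor do they show that the study is too small: for the named interaction under default settings it is larger than required. The drop-out slip is real but amounts to one person per group and is covered by the 48 planned.

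**What to change.** Rewrite the sample-size paragraph to:
- say whether 36 is the total or the number per group;
- name the primary contrast and outcome, in particular whether it is the group × task interaction on raw performance or the group comparison of the ratio dual-task cost, and over one modality or both;
- restate the calculation for that contrast with m, rho, epsilon and the convention for f;
- report the power or detectable effect at 36 completers per group. For a single dual-task-cost score this is f = 0.30 at 80% power (0.63 at f = 0.25). For hearing-impaired versus normal-hearing older adults it is d = 0.67 unadjusted, or 0.78 with Bonferroni for three pairs;
- change 44 to 45 per group for 20% drop-out.

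The cost is one reworded paragraph. The power reported for the main hypothesis may turn out less favourable than 0.80, depending on the contrast chosen. The target of 48 per group can stay.

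### The 20% drop-out allowance is computed as 36 × 1.2 (44 per group) when it should be 36/0.80 = 45; a minor error that fits within the 48 already planned

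*Protocol article*

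**What the plan says.** The section Sample Size Estimate/Power Calculations reports an a priori G*Power calculation ("repeated measures, within-between interaction, effect size f = 0.25", "alpha error prob = 0.05", "power (1-beta error prob) = 0.8", "number of groups = 3") and arrives at 36 per group. Two further figures follow. The first is the drop-out allowance: "Due to an expected drop-out rate of about 20 percent, we will integrate at least 44 participants for each group". The second is the recruitment aim: "We aim to recruit 48 participants per group for the Prescreening".

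The section Recruitment of Participants refers to the sample size calculation and says that "a group of 96 community-dwelling older adults (50–70 years) and 48 younger adults (20–30 years) will be recruited", with the older adults split equally by hearing status. The Abstract ties the same 48 per group to the calculation. The procedure for Measurement Day 1 makes clear that only participants who meet the inclusion requirements come back for day 2, when the single- and dual-task measurements are made.

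There are thus three numbers per group for three stages: 48 prescreened, at least 44 included, 36 needed for analysis.

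**The concern.** The step from 36 to 44 uses the wrong operation. A drop-out rate applies to the participants who start, so the number starting must satisfy n × (1 − 0.20) ≥ 36. Adding 20% to the number needed at the end gives too small an answer. A figure introduced as a minimum should meet the requirement under the plan's own assumed loss, and 44 does not.

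A secondary point is one of labelling. The Abstract and the recruitment section link 48 per group to the calculation without saying that it is the count before screening. A reader of those two places alone could take 48 as the number studied.

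At stake is the internal consistency of the sample size statement. The 80% power claim rests on 36 per group, and the stated inclusion minimum falls slightly short of supporting it.

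**Working it through.** **Inputs, all from Sample Size Estimate/Power Calculations:** required number per group 36; expected drop-out about 20%; stated minimum to include 44; prescreening aim 48.

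**1. Reproducing the plan's figure.** n × (1 + d) = 36 × 1.20 = 43.2, rounded up to 44. This matches the stated minimum exactly.

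**2. Correct allowance.** n / (1 − d) = 36 / 0.80 = 45 per group, or 3 × 45 = 135 in all, against 3 × 44 = 132 as stated. The difference is one participant per group.

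**3. Expected completers per group at exactly 20% loss.**

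| Entering | Calculation | Expected completers |
|---|---|---|
| 44 | 44 × 0.80 | 35.2 |
| 45 | 45 × 0.80 | 36.0 |
| 48 | 48 × 0.80 | 38.4 |

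**4. Loss that 44 can bear.** 1 − 36/44 = 0.182, so 36 remain only if drop-out is 18.2% or less.

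**5. Room for screen failures within 48.** 48 − 45 = 3 (3/48 = 6.25%) if 45 are to be included; 48 − 44 = 4 (4/48 = 8.3%) for the plan's own 44.

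**6. Effect on power of 35 instead of 36 per group.** The article states neither the number of repeated measurements nor their correlation, nor which G*Power effect-size option was used, so these are assumptions. With f = 0.25, alpha 0.05 and three groups, the noncentral F distribution gives:

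| Assumed setting | Power at 36 | Power at 35 | Difference (points) |
|---|---|---|---|
| 2 measurements, SPSS-type option | 0.6121 | 0.5983 | 1.4 |
| 2 measurements, Cohen option | 0.6251 | 0.6117 | 1.3 |
| 2 measurements, default option, correlation 0 | 0.9106 | 0.9021 | 0.9 |
| 2 measurements, default option, correlation 0.5 | 0.9976 | 0.9969 | 0.1 |

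Only the differences matter here. The levels show how strongly power depends on settings that the article does not state. The check takes 36 per group as given. The plan words that result both as a total and as a per-group number, which is a separate question that this correction does not touch.

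**The case against.** The strongest reply is that the error is trivial and the text already absorbs it. Drop-out is given only as approximate, and 18.2% could pass for about 20%. The 44 is a floor, so it does not exclude 45. Recruitment aims at 48, and 48 × 0.80 = 38.4 exceeds 36 if the 20% is meant to cover screening losses as well. All of this stands as an argument about size. It does not make 44 the right result of the stated inputs: a floor that meets the target only when loss is below the assumed rate is set one too low.

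Three stronger readings are tempting, and the article does not support them.

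- *A reader might infer that the plan will not deliver 36 completers.* That would need a screen-failure rate, and none is given. Assumed rates of 10% or 20% on 48 would give 34.6 (48 × 0.90 × 0.80) or 30.7 (48 × 0.80 × 0.80), but these are illustrations. The 48 is an aim, and nothing says that recruitment stops there. A binomial calculation with 80% completion gives a probability of at least 36 completers of 0.47 from 44, but still only 0.59 from the correct 45. A hard cut at 36 is therefore a poor measure of what is lost.
- *A reader might infer that the Abstract and the recruitment section contradict the sample size section.* They do not: all three speak of recruiting 48 per group. The first two omit that this is the count before screening.
- *A reader might infer that 48 per hearing group cannot be set in advance, because groups are allocated after the first session.* Eligibility Criteria has audiologists evaluate hearing severity before the prescreening session, and some recruitment runs through collaborating audiologists. Hearing status can therefore be known when participants are approached.

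**Conclusion.** The concern holds as a minor arithmetic error. From the plan's own 36 per group and 20% drop-out, the minimum to include is 45, not 44. At that loss, 44 entrants are expected to fall 0.8 of a participant short of 36 in each group. The cost in power is about 1 percentage point, and no more than 1.4 in the settings tried, which rest on assumed measurements, correlation and effect-size option. No conclusion of the study turns on it.

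The labelling of 48 in the Abstract and recruitment section is loose rather than inconsistent and deserves a small edit. The result assumes that the 20% applies to participants after inclusion, which is how the sample size section reads, since it applies the rate to reach 44 and then gives 48 separately for prescreening.

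**What to change.** In Sample Size Estimate/Power Calculations, replace the minimum of 44 with at least 45 (36/0.80) included per group. In the Abstract and in Recruitment of Participants, say that 48 per group is the recruitment target for prescreening, and that it leaves room for 3 screen failures per group if 45 are to be included.

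The cost is a change of wording. The required inclusion rises by one per group (three overall) and stays within the 48 per group already planned.
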